#### Randomization

Randomization of schools into the immediate intervention or delayed intervention control conditions will be carried out by a statistician using an automated computer program. Randomization will occur in two blocks of ten schools, at an equal one-to-one ratio. The statistician will keep the resulting group assignments in a downloaded file and restrict file access from the study team. The research team will be blinded to randomization during the recruitment process. Once a school is committed to the study (i.e., signed MOU), the statistician will inform the study team to which group the school has been randomized. Each school will be randomized in the order in which they commit to participating in the study.

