## Methods and analysis

### Design

We will recruit two cohorts of schools (*n* = 20 schools, total) to participate in a 9-month pilot cluster randomized controlled trial. The study design processes—including school recruitment, enrollment, and randomization, as well as student recruitment, data collection timepoint, and program participation—are illustrated in Figure 1 and described in detail below. Once a school agrees to participate, it will be randomized to receive the STHS intervention immediately or a delayed intervention condition (i.e., control group). The delayed intervention group will receive the curriculum to implement at their discretion, one school year after serving as a control. We will collect pre-(beginning of the academic year; T1) and post-test outcomes (end of the academic year; T2) for intervention and delayed intervention conditions. Additionally, for the intervention group, we will gather outcomes at 4 months (T3) and 12 months (T4) post-intervention to assess the short- and long-term maintenance of the intervention effects. The trial has been registered on clinicaltrials.gov (NCT05867433). The Institutional Review Board at Texas A&M University approved all measures, procedures, and protocols (IRB2023-0530D).

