### Selection of subjects

#### Recruitment

School recruitment will occur using a two-pronged approach. First, we will use the Texas Education Agency website to identify contact information for all middle schools in Texas that meet inclusion criteria (38). We will recruit schools using emails, phone calls, and information folders dropped off at eligible schools in Texas. Simultaneously, we will work with AgriLife Extension Family and Community Health and 4-H agents to identify schools that may be interested in participating in the study. We will hold in-person or virtual meetings with school representatives (e.g., school health advisory councils) to provide an in-depth program description. School administrators from all schools that enroll in the study will sign a memorandum of understanding (MOU) agreeing to participate.

Within schools, we will recruit 5th through 8th grade students (*n* = 20–25 students per school). Eighth-grade students will only be recruited in schools that also have an attached high school where eighth-grade students matriculate, so that they can be assessed at follow-up. Otherwise, we will not recruit 8th-grade students because their transition into high school could introduce new individual and/or environmental factors that may affect study outcomes. Likewise, we will only recruit 5th through 8th grade students from elementary schools if the grade does not matriculate into another school the following year. We will disseminate information for participating in the STHS program via school-wide announcements, flyers posted at the intervention schools, and school-sponsored events. Students and their parents will also receive an email with information about participating in the research study and information on how to contact the research team if they are interested in their student(s) participating. We will also host information sessions for parents and students before and after school, where they can ask more questions about the program. Prior to signing consent forms, the research team will screen participants for inclusion and exclusion criteria. If the student qualifies for the study, the parent will be asked to read and return a consent form. Students will be asked to assent to participate in all study procedures.

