#### Delayed intervention control group

The delayed intervention control group will continue with usual care during the first school year, as they will not be asked to add or remove any of their current physical activity, healthy eating, or positive youth development programming. During that year, students will be recruited to take part in data collection within 1 month of the student recruitment period (T1) and at the end of the school year (T2). After T1 and T2 data collection is complete, the control schools will receive the STHS intervention and $3,000, as described below, to implement at their discretion.

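### Students are enrolled after their school's arm is disclosed and under different offers, so randomising schools does not protect the comparability of the students analysed

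*Protocol article*

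**What the plan says.** The protocol article's Randomization section provides for 1:1 allocation in two blocks of ten schools. It states that "Each school will be randomized in the order in which they commit to participating in the study" and that, at the signed MOU, "the statistician will inform the study team to which group the school has been randomized". It also states: "The research team will be blinded to randomization during the recruitment process".

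The Design section lists the study steps as "including school recruitment, enrollment, and randomization, as well as student recruitment, data collection timepoint, and program participation", with student recruitment after randomization.

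The Recruitment section says: "We will disseminate information for participating in the STHS program via school-wide announcements, flyers posted at the intervention schools, and school-sponsored events". It adds an email to students and parents about the research study and information sessions for families. It has the research team screen students before consent.

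For the control arm, the Delayed intervention control group section says that during the control year "students will be recruited to take part in data collection within 1 month of the student recruitment period (T1"), with a second measurement at T2. These schools receive the program after T1 and T2.

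The Quantitative analysis section adjusts for the baseline score and for covariates picked up in preliminary bivariate analyses.

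**The concern.** In a cluster trial, randomisation balances the schools in expectation. It balances the students only if who enters is settled without reference to the arm. Here volunteers are enrolled once the arm is known, and what they are told they are joining appears to differ. One arm may attract students drawn to a health and civic club, and the other students willing to be measured.

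Positive youth development, one of the two primary outcomes, covers competence, confidence, character, connection and caring. These traits could plausibly be related to volunteering for such a club. Multiple imputation and an intention-to-treat analysis address what happens after entry. They do not repair a difference in who entered. The limitations in the Discussion cover variation in delivery and substitute programs in control schools, but not this.

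**Working it through.** The main question is one of sequence, so the sections are set side by side. Arithmetic applies only to the secondary point about blocks.

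**1. When is the arm known?** At the signed school MOU (Randomization).

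**2. When are students recruited?** Three places presuppose a known arm.
- Study eligibility defines eligible students by enrolment at a school that is receiving STHS or the control condition.
- Recruitment places flyers at intervention schools, which cannot be done before the arm is known.
- Delayed intervention control group describes recruiting students during the control year.

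The step order in Design agrees. Measures places T1 within one month of the student recruitment period. No section has students identified or consented before disclosure.

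**3. What does the blinding sentence cover?** If disclosure is at the MOU and students come later, a team blinded through recruitment can only be blinded through school recruitment. The same team later screens students.

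**4. Is the offer the same?** What the text shows is as follows.

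| Element | Intervention schools | Control schools |
|---|---|---|
| Program flyers | Yes | Not mentioned |
| Stated purpose of recruitment | Taking part in STHS; study participation separate and optional | Data collection at T1 and T2 |
| Research-study email, information sessions | Not restricted by arm | Not restricted by arm |
| Eligibility criteria, gift card per session | Same | Same |

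**5. Who is exposed?** 20 schools × 20 students = 400, and 20 × 25 = 500. That is every enrolled student and both primary comparisons.

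**6. What can adjustment do?** Positive youth development is measured at T1, and its baseline score enters the model. The student survey also covers theory-of-planned-behavior constructs and engagement with the school health environment, and these may be added as covariates. Selection that shows up in these scores can be adjusted for. Motivation that affects change over the year but is not captured by them cannot.

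**7. Blocks of ten, disclosed school by school (secondary).** With k = 5 schools per arm in a block of 2k = 10:
- The expected number of final schools whose arm is fully determined is 2k/(k + 1) = 10/6 = 1.67 per block, or 3.3 of 20 schools.
- The expected number of correct guesses, always guessing the arm with fewer schools so far, is 5 + (2^10/252 − 1)/2 = 5 + (4.06 − 1)/2 = 6.53 of 10, against 5 by chance. Here 252 is the number of ways to choose 5 of 10.

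These figures assume that someone knows the block size and keeps count. Bias would also require that the guess influence which school is approached or when its MOU is signed.

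**The case against.** The strongest reply is that program advertising and study recruitment are separate. The flyers concern the program, students may join STHS without joining the study, and the study has its own email with no stated restriction by arm. The information sessions are not restricted either. Eligibility criteria and the gift card are identical. The article does not give the wording of the control invitation, so it does not establish that control families hear nothing of the later program. No single sentence states the full order of events, and Figure 1, which illustrates it, is not available here.

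All of this stands as mitigation. It does not remove the problem. An email that is the same in both arms arrives, in one arm, alongside flyers for a program starting at that school. None of the safeguards conceals the arm from those who screen and enrol. The sections taken together leave little room for another order.

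Some stronger readings are tempting but not supported:
- **The arms are not comparable at baseline.** No data exist yet. The document shows only that comparability is unprotected.
- **Adjustment cannot help with motivation or engagement.** Several related measures are taken at T1. Only the unmeasured remainder escapes.
- **An assumed selection difference can be expressed as a share of the planned effect.** The effect size of 0.27 was set for abdominal obesity. A difference in health orientation is on another scale, and such a ratio ignores baseline adjustment.
- **Recruiters will exploit the block.** The list is withheld and nothing in the text suggests steering. The predictability is real but minor.

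It can also be said that this is a pilot offering initial evidence. But the article's stated aim is to test efficacy, and the weakness lies in enrolment, which no later analysis plan can undo.

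**Conclusion.** The concern holds as a risk of differential recruitment. Allocation is disclosed before students are recruited, screened and consented, and the two arms are described as recruited to different things. Comparability of the enrolled students is therefore not protected by randomising schools and cannot be assumed. The blinding statement protects school recruitment only.

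Every enrolled student is exposed, but neither the direction nor the size of any bias can be derived from the document, and no figure is offered. End-of-block predictability, about 3.3 of 20 schools on average, is a minor addition.

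The conclusion rests on the order of events inferred from the Design, Study eligibility, Recruitment, Randomization and Delayed intervention control group sections. It would fall only if students were in fact consented before the arm was disclosed, in which case the text should say so.

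**What to change.** **Schools not yet randomised**
- Use one identical, arm-neutral study invitation in all schools, stating that the school may receive the program now or a year later.
- Withhold each school's allocation from both the school and the study team until its consented student list is closed, preferably until T1 is complete.
- Advertise the STHS program only after that list is closed.
- Where the calendar allows, randomise and disclose each cohort's ten schools together. This also removes the predictability at the end of a block.
- Reword the blinding sentence to say which recruitment it covers.

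**Schools already randomised**
- Report the numbers approached, eligible and consenting, and baseline characteristics, by arm.
- Pre-specify adjustment for baseline positive youth development, theory-of-planned-behavior and engagement scores, rather than leaving these to bivariate screening.
- State recruitment bias as a limitation.

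**Cost**

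This needs a protocol amendment. Program start, and the naming of implementation leads and local student implementers, move somewhat later, leaving less of the school year for the 16 modules. Closing each school's list before disclosure is the cheaper version. Completing T1 first, or waiting for all ten schools in a cohort, gives better protection but takes more of the calendar.

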#### Delayed intervention control group

The delayed intervention control group will continue with usual care during the first school year, as they will not be asked to add or remove any of their current physical activity, healthy eating, or positive youth development programming. During that year, students will be recruited to take part in data collection within 1 month of the student recruitment period (T1) and at the end of the school year (T2). After T1 and T2 data collection is complete, the control schools will receive the STHS intervention and $3,000, as described below, to implement at their discretion.

### Interventional methods

#### Intervention development and refinement

As previously stated, STHS was developed by adapting Change Club, an evidence-based civic engagement program that aims to improve health behaviors and outcomes among adults in underserved communities by guiding individuals to create healthy environmental changes in their community. In our STHS adaptation, utilizing evidence-based intervention (EBI) mapping (39, 40), we adapted mechanisms of behavior change to utilize the theory of planned behavior as opposed to social cognitive theory, continued to focus on interpersonal social support, and narrowed the focus of environmental change from the community-level to the 10 domains of the Whole School, Whole Community, Whole Child (WSCC) model (Figure 2). Finally, we adapted the program to allow greater flexibility in delivery, considering the variability of instructional schedules across schools [i.e., structured 24-week program to 16 flexible 1-h modules (or 32 thirty-minute sessions)].

**Figure 2 F2:**
[figure not shown]
Strong teens for healthy schools-change club theoretical frameworks and expected outcomes.

Additional refinements were made to STHS by conducting preliminary qualitative interviews with intended program implementers—AgriLife Extension agents (*n* = 20) and middle school staff (*n* = 12) from Texas. Implementers provided feedback on the strengths and weaknesses of STHS's components (i.e., curriculum, resources, and training). This study is published elsewhere (41). Briefly, findings from this study emphasized the following: potential challenges due to variations in students' reading levels and understanding of key concepts, the need for implementer training and support to facilitate consistent delivery of the core curriculum components, adding alternative activities that could overcome school resource- and scheduling-related challenges, and the importance of activities and resources to actively engage students (41). These findings informed additional modifications made to refine STHS (Table 1).

**Table 1 T1:** Strong teens for healthy schools curriculum refinement from preliminary efforts.

**Issue**	**Change made to STHS**	**Data sources/reason**
Curriculum comprehension	Lowered the reading level, simplified key concepts and added examples after a concept is introduced (e.g., provided examples of assets like buildings and people).	In the **preliminary qualitative work** and **pilot testing**, extension agents and teachers discussed students' challenges with the reading level and lack of understanding of key concepts.
	Adding class engagement activities (e.g., thumbs up/down) to assess students' existing knowledge or their takeaways from curriculum topics.	In the **preliminary qualitative work**, extension agents and teachers emphasized the importance of student engagement, and in our **pilot testing**, research staff observed that students were not as engaged as we had hoped with the curriculum.
Curriculum structure	All lessons were structured as follows – overview, description of the topic with a “say” statement that emphasizes key points and provides additional talking points, activity, discussion questions, and reminders.	In our **pilot testing**, research staff observed inconsistency in session structure.
	Optional technology free activities—All sessions that required the use of technology were supplemented with an optional activity.	In our **preliminary qualitative work**, extension agents and teachers suggested a need for activities to fill additional time or replace activities that required technology. In the **pilot testing**, the teacher said some of the websites in the curriculum were blocked and that they didn't know how to use the classroom smart board until the end of year.
Additional resources	Complementary student workbooks were created for students to document and track progress on their project.	In the **pilot testing**, research staff observed that teachers had a hard time keeping track of important handouts related to the civic engagement project.
	The implementation guide's appendix was updated with resources, such as supporting videos to serve as a visual aid for key concepts (e.g., heart disease, mindfulness).	In the **pilot testing**, research staff observed that some of the videos in the curriculum were no longer available online.
Training	Research staff provide structured and comprehensive training	In our **preliminary qualitative work**, extension agents wanted more resources on how to work with students, and school staff discussed the importance of training to facilitate implementation. In the **pilot testing**, research staff observed a need for more structured training for teachers that could also be replicated if the STHS implementer switches during the year.
	Added a student implementer program where students at local colleges provide support to teach sessions. Student serves whatever role is needed as the lead educator deems appropriate (e.g., team-based teaching or classroom management support).	In the **preliminary qualitative work**, extension agents and school staff groups wanted a dedicated person to implement program. During **pilot testing**, the interviewed teacher wanted more support in implementing the session, and the research team ended up serving as additional support when they attended the observations. Additionally, the research team noticed a need for continuity when an implementer wasn't available or switched during the program.

STHS, Strong Teens for Healthy Schools.

We also pilot-tested STHS at one school (*n* = 5 students) as part of an after-school program. During pilot testing, the research team observed five STHS sessions, taking observational notes and having informal discussions with the teacher implementing the program. The teacher also participated in a structured interview, providing feedback about their experience delivering STHS. The research team's observations and informal discussions with the teacher revealed issues with student engagement, challenges with technology-based activities, inconsistency in session structure, difficulties with keeping track of important handouts related to the civic engagement project, and the need to create a contingency plan when an implementer was unavailable or left during the program. Like the implementer interviews described above, both research team observations and the teacher interview revealed potential challenges due to variations in students' reading levels and understanding of key concepts, as well as the need for implementer training and support to facilitate the consistent delivery of core curriculum components. These findings also informed additional modifications made to refine STHS (Table 1).

#### Intervention content

For this study, STHS includes 16 one-hour modules, which could also be delivered as 32 thirty-minute sessions to provide flexibility, that provide education and activities on civic engagement, healthy eating, and physical activity (Table 2). Additionally, students will set healthy eating and physical activity goals using the Specific, Measurable, Achievable, Relevant, and Time-bound (SMART) goal approach and receive support for maintaining individual-level healthy eating and physical activity behaviors. They will also identify, plan, and implement a school health environmental change project. Each STHS school will receive a $3,000 stipend to support the health environmental change project(s).

**Table 2 T2:** Overview of strong teens for healthy schools curriculum topics.

**Module**	**Type**	**Session tile (30 min)**	**Activities**
1A	CE	Introduction & fostering engagement	1.1 Program overview 1.2 Strong teens bingo (i.e., icebreaker) 1.3 Setting club rules 1.4 Activity on the types of environmental change
1B	PA	Importance of physical activity	1.5 Types of physical activity discussion 1.6 SMART goal setting for physical activity 1.7 Fitness charades (i.e., active game) 1.8 Extended activity (i.e., try a new type of physical activity at home)
2A	CE	Team building	2.1 Cup stacking challenge (i.e., team building) 2.2 Advocacy gallery walk (i.e., activity to identify personal interests)
2B	HE	Healthy eating basics	2.3 Kahoot about healthy eating 2.4 SMART goal setting for healthy eating 2.5 Extended activity—download MyPlate Plan App to use at home
3A	CE	PhotoVoice projects	3.1 Photovoice part I (i.e., students complete an audit of their school health environment) 3.2 Small group discussion on photos taken
3B	PA	Facilitators & barriers to physical activity	3.3 Physical activity SMART goal check-in 3.4 Step awareness (i.e., activity that discusses how the environment affects physical activity). 3.5 Facilitators & barriers relay race (i.e., activity that discusses barriers and facilitators for physical activity)
4A	CE	Choosing a strategy & advocacy skills	4.1 Examples of environmental change projects 4.2 Create school change vision board
4B	HE	Supports & challenges to healthy eating	4.3 Healthy eating SMART goal check-in 4.4 Stand up sit down (i.e., activity to assess sugar knowledge) 4.5 Nutrition facts label—sugar 4.6 Grab & Go (i.e., activity that discusses barriers and facilitators for healthy eating)
5A	CE	Identifying stakeholders	5.1 Identifying stakeholders for environmental change 5.2 Contacting stakeholders for environmental change
5B	PE	Types of fitness	5.3 Physical activity SMART goal check-in 5.4 Fitness rotation (i.e., activity to discuss three types of fitness—aerobic, muscular strength/endurance, flexibility)
6A	CE	Asset mapping	6.1 School asset mapping 6.2 Personal asset mapping 6.3 Stakeholder check-in
6B	HE	Fruits, vegetables, & whole grains	6.4 Healthy eating SMART goal check-in 6.5 Mystery bucket (i.e., matching foods to their MyPlate category) 6.6 Nutrition facts label—dietary fiber
7A	CE	Leadership development	7.1 Leadership qualities discussion 7.2 Sneak-A-Peak activity (i.e., activity that focuses on problem solving and communication) 7.3 Designating group roles 7.4 Stakeholder check-in
7B	PA	Heart health	7.5 Physical activity SMART goal check-in 7.6 Heart health exploration (i.e., discuss how physical activity affects the heart) 7.7 Mindful walking
8A	CE	Vision planning	8.1 Develop mission statement for project 8.2 Create logic model for project
8B	HE	Proteins, fats, & dairy	8.3 Healthy eating SMART goal check-in 8.4 Nutrition facts label—fats 8.5 Healthy eating jeopardy 8.6 Optional activity—the ingredient game (i.e., create healthy meals using random recipe cards)
9A	CE	Action planning	9.1 Would You rather activity (i.e., activity for students to think about personal preferences for physical activity and healthy eating). 9.2 Develop action plan for project
9B	CE	Evaluation & monitoring	9.3 The blind polygon (i.e., game to teamwork, goal alignment, and organization skills) 9.4 Develop evaluation plan for project
10A	CE	Resources & support	10.1 Evaluate resources needed project 10.2 Project check-in #1 10.3 Optional activity—Papa's Sushiria Online Game (i.e., time management game)
10B	PA	Physical activity & SMART goals	10.4 Physical activity SMART goal check-in 10.5 Race for the truth (i.e., activity to visual social norms around physical activity).
11A	CE	Leadership development	11.1 Project check-in #2 11.2 Leaders You admire activity (i.e., activity to discuss leadership characteristics) 11.3 Silent leadership game (i.e., activity to discuss leadership characteristics) 11.4 Extended activity—community bingo (i.e., meet local leaders)
11B	HE	Healthy eating & SMART Goals	11.5 Healthy eating SMART goal check-in 11.6 Whyville snack shack games (i.e., game to read nutrition label) 11.7 Optional activity—food charades
12A	CE	Project implementation	12.1 Time squared (i.e., time management activity) 12.2 Project work time 12.3 Extended activity—community bingo check-in
12B	HE	Physical activity & SMART goals	12.4 Physical activity SMART goal check-in 12.5 Physical activity Cube (i.e., game to learn about active breaks) 12.6 Optional activity—quick thinks (i.e., review different types of physical activity)
13A	CE	Project implementation	13.1 Paper airplane (i.e., leadership and communication game) 13.2 Project work time
13B	PA	Healthy eating & SMART goals	13.3 Healthy eating SMART goal check-in 13.4 Breakfast around the world (i.e., MyPlate education about breakfast in different countries) 13.5 Optional activity—Food Knockout (i.e., game to review healthy foods)
14A	CE	Resources	14.1 Desert island game (i.e., game to learn about prioritization) 14.2 Project work time 14.3 Extended activity—Cake Mania Online Game (i.e., online time management game)
14B	CE	Project implementation	14.4 Colored pieces (i.e., game to learn about prioritization) 14.5 Project work time
15A	CE	PhotoVoice projects	15.1 Photovoice part II (i.e., students complete an audit of their school health environment and discuss changes over the year) 15.2 Small group discussion on photos taken
15B	CE	Project implementation	15.3 Final project work time 15.4 Optional Activity—find the Ace of Spades (i.e., time management and planning game) 15.5 Extended activity—final community bingo—check-in
16A	CE	Final SMART goal check-ins project reflections	16.1 Final SMART goal check-in 16. 2 Reflection snowballs (i.e., game to reflect on project) 16.3 Reflection discussion
16B	ALL	Project presentations awards ceremony	16.4 Project presentation 16.5 Awards ceremony

Extended activities are things that youth can do at home. Optional activities can replace the main activities in the curriculum. CE, civic engagement; HE, healthy eating; PA, physical activity.

